## Methods and analysis

### Socially assistive robot Pepper

The Pepper robot, developed by SoftBank Robotics, is a 120 cm tall social humanoid robot optimized for human interaction and engaging with people through conversation and a touch screen. It is capable of natural movement, navigation, speech recognition, and dialogue, and is equipped with perception modules and various sensors for multimodal interactions (e.g., microphones, infrared sensors, cameras, and sonars). These functions allow for smooth interaction that does not require any specific training. The Pepper robot also has several safety mechanisms, such as bumper sensors, that prevent it from physically harming participants (29). For the purposes of the proposed study (and other studies within the H2020 project HosmartAI), the robot was taught to understand and express gestures, facial expressions, and speech in the Slovenian cultural context and language. It was also taught to perform exercises and scenarios that are part of the intervention (see section “Study design”).

The robot was first extensively tested in a laboratory setting. After this stage, we introduced the robot to employees in both participating departments. The robot was then extensively pilot tested on-site over the period of 3 months, with significant input from the clinical staff.

Despite extensive pilot testing, Pepper will be constantly supervised throughout the study by at least one researcher, enabling us to detect failures immediately and make quick repairs if needed. In the case of more severe malfunctions, the robot will be temporarily replaced with a backup unit. Moreover, in the rare event of the second unit also malfunctioning, the study will be temporarily put on hold and participants from the interrupted iteration will be excluded from analyses. The study will continue when at least one robot is working properly again.

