### Study design

The proposed study employs a between-within interaction design with multiple iterations. Patients and employees participating in the study will be recruited in a University Clinical Centre Maribor, Slovenia. The study will be carried out in 1-week intervals, followed by a 1-week washout period between each iteration. Overall, the study will be conducted over 2 years or less if the desired sample size is reached sooner.

Patients admitted to vascular and thoracic surgery wards for an elective (non-emergency) procedure will be screened for eligibility regarding the inclusion and exclusion criteria. Eligible participants will then be informed about the study characteristics and asked to fill out an informed consent form. Those who will consent to participate in the study will participate for 3–5 days. Depending on the week (see Figure 1), participants will be allocated to the standard care group (i.e., a control group that will not interact with a socially assistive robot) or standard care group with additional robot interactions. Participants from both groups will first be informed about the study and fill out the baseline questionnaires (demographic data, engagement, and perceived quality of care). Similarly, participants from both groups will be subjected to standard nursing education and general/respiratory physiotherapy delivered by nursing and physiotherapy staff. However, the patients allocated to the standard care group with additional robot interactions will additionally be subjected to nursing education and general/respiratory physiotherapy delivered by a socially assistive robot. Moreover, they will be able to call the robot for additional assistance (not related to nursing education and physiotherapy) during the whole study period. At the end of their participation, patients from both groups will be asked to fill out the questionnaires (engagement, perceived quality of care) for the second time. Patients from both groups will also be asked to rate the education and physiotherapy they received during the study period. Moreover, patients that will interact with a socially assistive robot, will also fill out the User Experience Questionnaire (30) at the end their participation.

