**FIGURE 1 F1:**
[figure not shown]
Study design: patients.

The study will be conducted in several 1-week iterations with a washout period between them (to provide enough time for new patients to be admitted). Specifically, patients will receive standard care in week 1, followed by a washout period in week 2. Patients in week 3 will then receive standard care together with robot interactions, followed by a washout period in week 4. In week 5, patients will again receive standard care. The study procedure (for patients) is outlined in Figure 1. It is worth noting that all additional variables (e.g., number of interactions with a robot) will be collected continuously during each relevant iteration. Additionally, the instructions of all self-report questionnaires will be adapted to reflect the chosen time periods and tasks. Throughout the study, patients will be observed for signs of high distress and excluded from the study if needed.

In terms of intervention content, the nursing education will contain critical information on wound care, home care considerations, and daily care explanations. On the other hand, general and respiratory physiotherapy will consist of selected instructions and exercises that can be delivered both by a human and a robot. The AI-delivered nursing education and physiotherapy instructions will employ elements of gamification.

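### Dropping iterations in which both robots fail is a post-allocation exclusion that can fall only on the robot arm, and it risks a small overstatement of the robot's effect

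*Protocol article*

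**What the plan says.** The section on the robot sets out three levels of failure. A researcher is always present, "enabling us to detect failures immediately and make quick repairs if needed". Next, "In the case of more severe malfunctions, the robot will be temporarily replaced with a backup unit". Neither of these leads to any exclusion. The third level is failure of the backup as well, which the article calls rare and which pauses the study. Its consequence for the data is that "participants from the interrupted iteration will be excluded from analyses".

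Under Study design, the arm is set by the calendar: "Depending on the week (see Figure 1), participants will be allocated to the standard care group" or to the robot group. The standard care group is described as "a control group that will not interact with a socially assistive robot".

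A second rule follows in the description of the patient procedure: "Throughout the study, patients will be observed for signs of high distress and excluded from the study if needed". It is written for patients in general. It gives no criterion and does not say whether data already collected are dropped.

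A third exclusion, under Preliminary analyses, removes anyone with more than 20% missing values in any questionnaire. The article names no analysis of all allocated patients alongside these rules.

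**The concern.** The failure rule is an explicit statement about who is analysed, not a detail left to a fuller document. It acts after consent and allocation, and it has no counterpart in the control arm because a standard care week has no robot to lose. It removes the whole iteration, including patients who had days of robot contact before the breakdown and patients who had already finished.

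The Introduction and Discussion present the study as evidence on a robot placed on working wards, and H5 and H6 contrast periods with and without deployment. Downtime is part of deployment. If perceived quality of care or engagement suffers when the robot disappears mid-stay, the rule deletes those results from the robot arm, and the H3 and H4 contrast answers a narrower question than the one posed.

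The rule speaks of participants, not patients. If that includes staff and the failed week is the one that ends in T2, it also removes the measurement on which the paired tests for H5 and H6 depend.

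**Working it through.** **1. Which exclusions are one-sided**

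| Rule | Trigger | Arms it can affect |
|---|---|---|
| Minor or first-unit failure | Repair or backup unit | No exclusion |
| Interrupted iteration | Both units fail | Robot weeks only, in practice |
| High distress | Observation during participation | Both |
| Over 20% missing in any questionnaire | Data cleaning | Both, but only robot patients complete the User Experience Questionnaire |

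**2. The plan's sample size.** Inputs from Participants and recruitment: f = 0.15, two groups, m = 2 measurements, α = 0.05, power 0.80. The correlation ρ is not stated. For the group-by-time interaction, λ = f²·N·m/(1−ρ), with 1 and N−2 degrees of freedom. At ρ = 0.5 and N = 90, λ = 0.0225 × 90 × 2/0.5 = 8.1 and power is 0.804, so the stated 90 is reproduced. Other values of ρ would require 178 (ρ = 0), 126 (0.3) or 56 (0.7). The sample size is not in dispute.

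**3. The same effect on the change score.** With equal arms, λ = (N/4)·d², so d² = 8.1/22.5 = 0.36 and d = 0.60 SD of the change score.

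**4. Effect of dropping failed iterations.** Let q be the share of robot patients in dropped iterations and e the effect in those weeks. The all-allocated effect is (1−q) × 0.60 + q·e, and the overstatement is q × (0.60 − e). Both q and e are assumptions.

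| q | e = 0.60 | e = 0 | e = −0.3 |
|---|---|---|---|
| 2% | 0 | 0.012 | 0.018 |
| 5% | 0 | 0.030 | 0.045 |
| 10% | 0 | 0.060 | 0.090 |

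For scale, each four-week cycle contains one robot week, so two full years hold about 104/4 = 26 robot weeks. With equal recruitment per week, losing one of them removes 1/26 = 3.8% of robot patients. Earlier completion would make one week a larger share.

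**5. Distress exclusion.** This was simulated with no true effect, 45 patients per arm and 20,000 runs, removing the most distressed patients. The correlation between distress and change score was assumed to be 0.5.

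| Removed, robot vs control | Bias (SD) | Type I error |
|---|---|---|
| 5% vs 5% | 0.003 | 0.050 |
| 5% vs 2% | 0.026 | 0.050 |
| 5% vs 0% | 0.056 | 0.058 |
| 10% vs 0% | 0.098 | 0.071 |

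With a correlation of 0 there is no bias in any row.

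**6. Power.** With 45 controls and d = 0.60, losing 3 robot patients without replacement gives 0.790, losing 5 gives 0.779, and losing 9 gives 0.755. At 45/26 = 1.7 robot patients per week, two lost weeks cost between 3 and 4 patients.

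**The case against.** The strongest reply is that the trigger is narrow. Ordinary faults are repaired, a severe fault brings in the backup, and only a double failure, which the article calls rare, leads to exclusion. Most imperfect delivery therefore stays in the robot-arm data. That stands, and it is why the size is small.

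A hardware failure also removes a whole week regardless of how its patients were doing, so it is not selection on outcome. That stands too. A reader might infer that the comparison is biased, but the documents support only a risk: the shift depends on failed-week patients doing worse, and no passage shows that they would.

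A reader might also infer that the distress rule is one-sided. Its wording covers both arms, and it excludes from the study without saying that collected data are discarded. Unequal removal is possible because exposure differs and the arm is known, but it is not documented.

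Nor do the documents support a material loss of power. They give no number of patients per week, the study resumes after a failure, and recruitment may run for up to two years towards the target.

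On staff, the article does not say that they are dropped. The planned tests for H5 and H6 use only T1 and T2, so losing T4 or T6 would leave those tests unchanged.

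Finally, H3 and H4 are worded around exposure to robot-delivered care, and an analysis of delivered iterations fits that wording. This supports keeping such an analysis, but not making it the only one when the stated aim concerns a deployed robot.

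**Conclusion.** The point holds in a limited form. The failure exclusion comes after allocation, is one-sided in practice, and moves the H3 and H4 comparison from a deployed robot to a working one. The same applies to H5 and H6 only if staff count as participants and the T2 week is the one lost.

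The likely direction favours the robot. With 2–5% of robot patients removed and a failed-week effect of 0 to −0.3 SD, the overstatement is about 0.01–0.05 SD. That is 2% to 7.5% of 0.60 SD (0.012/0.60 and 0.045/0.60), and it is nil if failed-week patients fare equally well. The removal share, the failed-week effect and the correlation of 0.5 behind the 0.60 SD are assumptions, not figures from the article.

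The distress rule adds bias only if its rate or its link to outcome differs by arm. This is a modest defect, worth correcting before data are seen because the correction is nearly free.

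**What to change.** Replace the failure exclusion with a rule such as: *All consented patients and staff are analysed according to the week of allocation, whatever robot exposure they received. The second questionnaire is collected as planned in interrupted weeks and, where the patient agrees, after withdrawal for distress.* Then:

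- Keep the analysis without interrupted iterations as a sensitivity analysis.
- Report malfunctions, interrupted iterations and distress withdrawals by arm.
- Say what happens to the staff comparison if the T2 week is interrupted.
- Reconcile the new rule with the 20% missing-data exclusion, which would otherwise remove some of the same patients again. Say in particular whether the User Experience Questionnaire counts towards it, since only robot patients complete that form.

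The cost is a few sentences and a few more short questionnaires. The estimated effect may be slightly smaller. Who is withdrawn from robot interaction, and when, does not change; only who is analysed does.

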### Study design

The proposed study employs a between-within interaction design with multiple iterations. Patients and employees participating in the study will be recruited in a University Clinical Centre Maribor, Slovenia. The study will be carried out in 1-week intervals, followed by a 1-week washout period between each iteration. Overall, the study will be conducted over 2 years or less if the desired sample size is reached sooner.

Patients admitted to vascular and thoracic surgery wards for an elective (non-emergency) procedure will be screened for eligibility regarding the inclusion and exclusion criteria. Eligible participants will then be informed about the study characteristics and asked to fill out an informed consent form. Those who will consent to participate in the study will participate for 3–5 days. Depending on the week (see Figure 1), participants will be allocated to the standard care group (i.e., a control group that will not interact with a socially assistive robot) or standard care group with additional robot interactions. Participants from both groups will first be informed about the study and fill out the baseline questionnaires (demographic data, engagement, and perceived quality of care). Similarly, participants from both groups will be subjected to standard nursing education and general/respiratory physiotherapy delivered by nursing and physiotherapy staff. However, the patients allocated to the standard care group with additional robot interactions will additionally be subjected to nursing education and general/respiratory physiotherapy delivered by a socially assistive robot. Moreover, they will be able to call the robot for additional assistance (not related to nursing education and physiotherapy) during the whole study period. At the end of their participation, patients from both groups will be asked to fill out the questionnaires (engagement, perceived quality of care) for the second time. Patients from both groups will also be asked to rate the education and physiotherapy they received during the study period. Moreover, patients that will interact with a socially assistive robot, will also fill out the User Experience Questionnaire (30) at the end their participation.

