**FIGURE 2 F2:**
[figure not shown]
Study design: staff. This figure depicts only the first two measurements. The same protocol will be carried out at the 1-year mark and right before the end of the study (approximately 2 years after the beginning).

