### Participants and recruitment

The proposed study intends to recruit two distinct samples: patients and staff. The patient sample will be composed of patients admitted to vascular surgery and thoracic surgery wards for an elective (non-emergency) procedure. Beyond the type of disease for patients, patients need to be aged 18 years or above and willing to participate in the study. On the other hand, exclusion criteria include emergency patients, patients already enrolled in other studies, patients with dementia, special needs or appointed guardians, and patients allocated to an intensive step-down unit and/or regimen.

The staff sample will be composed of nursing and physiotherapy staff working on either the vascular surgery or the thoracic surgery ward. Again, only employees aged 18 years or above, who have signed a consent form, will be invited to participate in the study.

To minimize background noise while ensuring that all patients also receive standard care, the study will employ a between-within interaction design, whereby patients will be allocated either to the (1) standard care group or (2) standard care with additional robot interactions. We performed the sample size calculation in the G*Power software (31), choosing the ANOVA repeated measures with within-between interaction (2 groups, 2 measurements) as the statistical test, entering a small-to-medium effect size (*f* = 0.15), and choosing a conventional significance threshold and power (α = 0.05, 1-β = 0.80). Such calculations suggest that approximately 90 patients need to be recruited overall.

The nursing and physiotherapeutic staff will be studied with a simpler within-subjects design, whereby all consenting employees will fill out the questionnaires after a period of standard care and after the use of a socially assistive robot. As such, we performed the sample size calculation in the G*Power software, choosing the Paired-samples *t*-test as the statistical test, entering a medium effect size (*d* = 0.50), and choosing a conventional significance threshold and power (α = 0.05, 1-β = 0.80). Such calculations suggest that at least 34 nursing and physiotherapeutic employees must be recruited overall.

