#### Analyses of patient-related outcomes

The patient-related outcomes, specifically patient engagement (H1, H3) and perceived quality of care (H2, H4), will primarily be analyzed with two separate mixed-design (split-plot) analyses of variance (ANOVA), with group as the between-subjects factor (2 groups: standard care, standard care with robot interactions) and time as the within-subjects factor (2 levels: T1 and T2; see Figure 1). Significant results will be followed up with *post hoc* tests using the correction to adjust for multiple testing. All results will be accompanied by effect sizes.

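### Arms are assigned to whole calendar weeks, but the patient ANOVA and the 90-patient sample size treat patients as independent; any within-week correlation of change would understate the standard error for H3 and H4

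*Protocol article*

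**What the plan says.** All references are to the Protocol article.

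- **Allocation (Study design).** The arm follows the calendar: "Depending on the week (see Figure 1), participants will be allocated to the standard care group" or to standard care plus robot. The text after the Figure 1 caption gives a fixed order, with standard care in week 1, then "Patients in week 3 will then receive standard care together with robot interactions, followed by a washout period in week 4", then standard care again in week 5. Each patient takes part for 3–5 days, so belongs to one study week.
- **Timetable (Study design; Figure 2 caption).** Active weeks alternate with washout weeks of the same length. On total duration, the article says: "Overall, the study will be conducted over 2 years or less if the desired sample size is reached sooner". The staff schedule places its last measurements "right before the end of the study (approximately 2 years after the beginning".
- **Analysis (Analyses of patient-related outcomes).** Two mixed-design ANOVAs, "with group as the between-subjects factor (2 groups: standard care, standard care with robot interactions", and time (T1, T2) within subjects. Week does not appear.
- **Sample size (Participants and recruitment).** G*Power, "choosing the ANOVA repeated measures with within-between interaction (2 groups, 2 measurements) as the statistical test", with f = 0.15, α = 0.05 and power 0.80, giving about 90 patients. No design effect is applied.
- **Limitations (Discussion).** The authors say a larger randomized trial may be needed. They do not mention allocation by week or clustering.

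**The concern.** Everyone enrolled in a given active week is in the same arm, so the week is the unit of allocation. An ANOVA with group and time only takes its error term and degrees of freedom from patients. If some weeks go better or worse for all their patients, for instance through staffing or ward occupancy, that variation ends up in the group comparison and the error term does not reflect it.

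H3 and H4 concern the group-by-time interaction, that is, the difference between arms in T2–T1 change. A week effect that moves T1 and T2 equally cancels, so only the within-week correlation of change matters. Such correlation is plausible. T1 is completed before the study-week education and physiotherapy and T2 at the end of participation, and the PQMC asks about care that patients in the same week partly share.

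At stake are the nominal 5% level of the two between-group patient hypotheses and the power claimed for 90 patients.

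**Working it through.** **Inputs from the article:** N = 90, f = 0.15, α = 0.05, two measurements, alternate active weeks, up to 2 years.

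**Assumed, because not stated:** T1–T2 correlation ρ; within-week ICC of change (0.01 to 0.10); patients per week m; continued one-to-one alternation after week 5; equal week sizes (unequal sizes would raise the design effect).

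**1. Reproduce N = 90.** For the within-between interaction, λ = f²·N·2/(1−ρ), with 1 and N−2 degrees of freedom. At ρ = 0.5, λ = 0.0225 × 90 × 2 / 0.5 = 8.1, and power on 1 and 88 df is 0.804. The stated N is recovered with almost no margin. With f held at 0.15, the N needed would be 178 at ρ = 0, 126 at ρ = 0.3 and 56 at ρ = 0.7, so the 80% figure rests on ρ as well as on independence. In SDs of change, λ = d²·N/4 gives d² = 4 × 8.1/90 = 0.36, so d = 0.60.

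**2. Number of weeks.** Two years is 104 calendar weeks, so about 104/2 = 52 active weeks, and 90/52 ≈ 1.7 patients per week. At 5 per week, 18 active weeks suffice; at 9 per week, 10.

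**3. Allow for clustering.**
- Design effect: DE = 1 + (m−1)·ICC.
- Type I error of the unadjusted test: about 2[1 − Φ(1.96/√DE)].
- Power at a valid 5% level: noncentral F with λ = 8.1/DE on 1 and (weeks − 2) df.

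Example, 10 weeks and ICC 0.05: DE = 1 + 8 × 0.05 = 1.40; 1.96/√1.40 = 1.66, so type I error is 9.8%; λ = 8.1/1.40 = 5.79 on 1 and 8 df, so power is 56%.

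| Active weeks | m | ICC | DE | Type I error, unadjusted | Power at a valid 5% level |
|---|---|---|---|---|---|
| 52 | 1.7 | 0.01 | 1.01 | 5.1% | 79% |
| 52 | 1.7 | 0.05 | 1.04 | 5.4% | 78% |
| 52 | 1.7 | 0.10 | 1.07 | 5.8% | 77% |
| 18 | 5 | 0.05 | 1.20 | 7.4% | 68% |
| 18 | 5 | 0.10 | 1.40 | 9.8% | 62% |
| 10 | 9 | 0.05 | 1.40 | 9.8% | 56% |
| 10 | 9 | 0.10 | 1.80 | 14.4% | 46% |

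**4. Simulation check.** Change scores with a week random effect and d = 0.60, comparing a patient-level t-test (equivalent to the planned interaction test) with a t-test on week means. In the 18- and 10-week cases, type I error of the patient-level test was 7.2% and 9.9% (18 weeks, ICC 0.05 and 0.10) and 9.8% and 14.4% (10 weeks). The week-mean test held about 5%, with power of 68%, 62%, 56% and 46%. When the effect is real, the patient-level test still rejects about 74–78% of the time in these four cases.

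Part of the power loss with few weeks comes from degrees of freedom alone. At ICC 0 the week-mean test has about 76% power with 18 weeks and 70% with 10.

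**The case against.** A reader might infer that the p-values will be too small and that 80% power will not be reached. The article does not support that as a certainty. Both consequences need a positive ICC of change and more than a patient or so per week, and it gives neither figure. Its timetable points to the mild case: staff are measured at the start, at 1 year and near 2 years. Reaching 90 patients in 18 active weeks would take about 2 × 18 − 1 = 35 calendar weeks, and in 10 active weeks about 19, both before the 1-year staff measurement. This stands. However, the article sets no minimum number of weeks and explicitly allows an early finish, so the worse cases remain open.

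The mechanism can also be overstated. Staff work in both kinds of week, patients come from two wards, and stable week effects cancel in the change score. A shared robot unit or supervising researcher would be inference: the article requires at least one researcher, provides a backup robot, and uses no robot in control weeks. These points argue for a small ICC, not for zero.

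Nor should the 46–68% figures be read as the rejection rate of the planned ANOVA. They are power at a true 5% level. The planned test rejects more often, at the cost of a higher false-positive rate.

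**Conclusion.** The mismatch is established by the text: allocation is by week, while analysis and sample size are by independent patient. Its consequence is conditional. On the full timetable of about 52 active weeks it is small: type I error is at most about 5.8% and valid power at least about 77% for ICC up to 0.10. If recruitment is concentrated in few weeks it is material: at ICC 0.05–0.10, about 7–10% and 62–68% at 5 per week, and about 10–14% and 46–56% at 9 per week. All these figures assume f = 0.15, ρ = 0.5, equal week sizes and continued alternation.

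The stated 80% at N = 90 should therefore be presented as holding for a week ICC of change of 0 and a T1–T2 correlation of about 0.5. The change is worth making because it is cheap and protects the analysis whichever way recruitment goes.

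**What to change.** 1. Record the study week (iteration) for every patient.
2. Analyse PHE and PQMC with a linear mixed model, for example on the T2–T1 change, with arm as a fixed effect, a random effect for study week, and Satterthwaite or Kenward-Roger degrees of freedom. If both time points are modelled instead, the week effect must be allowed to differ by time, since a plain week intercept cancels from the interaction. An analysis of week-mean changes, weighted by patients per week, is an acceptable alternative.
3. Restate power as conditional. Give the assumed T1–T2 correlation, the expected number of active weeks and patients per week, and 1+(m−1)ICC over a range of ICC.

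**Cost:** changed model wording, slightly wider intervals and a less favourable stated power. With only one or two patients per week the week variance will be poorly estimated, but that is also where it matters least. No weekly enrolment cap is needed; it would conflict with the stated intention to invite all eligible patients.
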